## Abstract

**Background:**

Among university students, the experience of academic stress is associated with symptoms of anxiety and depression. Single-session interventions (SSIs) are structured and accessible self-guided interventions, often delivered digitally, that integrate elements of empirically supported treatments. Compassion-Focused Therapy (CFT) has been shown to be beneficial in alleviating stress, anxiety, and depression. However, the effectiveness of CFT (1) in the academic context, and (2) when delivered in brief digital formats, has not yet been tested.

**Objective:**

This study aims to evaluate the effectiveness of a compassion-focused online SSI for reducing stress among university students.

**Methods:**

University students aged 18‐65 years that indicate at least mild stress (a score >7 on the stress scale of the Depression Anxiety Stress Scale–21 [DASS-21]) will be recruited from German-speaking Switzerland. The target sample size is 156 participants randomly assigned to either the intervention or the waitlist control group. The 45-minute intervention follows the typical SSI structure and combines psychoeducation on academic stress, core CFT principles, guided breathing, compassion imagery exercises, and includes an action plan. Assessments will be conducted at baseline, 24 hours after the intervention, and at the 1-week follow-up. The primary outcome is the change in stress between baseline and 1-week follow-up, measured with the stress scale of the DASS-21. Secondary outcomes include depressive symptoms and anxiety measured with the depression and anxiety scales of the DASS-21 between baseline and 1-week follow-up. Data will be analyzed using linear (mixed-effects) models.

**Results:**

Ethical approval for the study was received in September 2025. Recruitment and data collection started in November 2025; data collection will conclude once 172 participants have been enrolled. As of April 15, 2026, 67 participants have been enrolled. Data analysis is planned for winter 2026, with the primary findings being prepared for publication in the spring of 2027.

**Conclusions:**

To our knowledge, this study is the first randomized controlled trial to examine the effects of a compassion-focused online SSI on reducing stress in university students. If the program proves to be effective, it would offer a low-threshold, cost-effective, and scalable mental health intervention for the academic context.

## Introduction

### Academic Stress in University Students

According to Lazarus and Folkman [1], stress arises when individuals perceive a discrepancy between the demands of a situation and their available resources. In the academic context, students often experience stress when the perceived demands of heavy workloads, tight deadlines, and high-performance expectations exceed their available coping resources [2,3]. Psychological contributors to academic stress include fear of failure, perfectionism, and self-criticism [4]. These are associated with maladaptive coping responses such as avoidance, overcompensation, or emotional suppression [4,5].

Recent studies from Germany report high levels of strain among university students, with more than 30% experiencing frequent depressive symptoms, more than 40% having difficulties with concentration and decision-making, and around 40% to 50% feeling exhausted or showing signs of burnout [6,7]. The proportion of students who perceive negative effects of academic stress on their health varies by gender, with almost 40% of students who identify as female, two-thirds of students as gender-diverse, and 28% of students as male reporting affected health [6,8]. In the Netherlands, a survey of 224,000 university students found that 39.8% experienced high stress related to their academic workload, 68% felt psychologically burdened by study demands, and 35% reported frequent loneliness, with 6.9% reporting the experience to be severe [9]. Similar patterns were found in Switzerland, where a cross-sectional study among 915 university students revealed that lower academic satisfaction was strongly associated with higher levels of perceived stress, symptoms of anxiety, and depression [10]. These high prevalence rates of psychological distress coincides with persistently underresourced student support services [11,12], reflecting a significant treatment gap for university populations [13].

### Interventions to Counter Academic Stress

Meta-analytic evidence shows that cognitive, behavioral, and mindfulness-based interventions effectively reduce anxiety, depression, and physiological stress responses among university students [14]. Recent findings highlight the benefits of mindfulness, acceptance, and self-compassion components in improving emotional regulation and reducing self-critical thought patterns [15]. However, few approaches explicitly target fear of failure and self-criticism, key psychological drivers of academic stress. Compassion-Focused Therapy (CFT) directly addresses these mechanisms by cultivating self-compassion and balancing affiliative and threat-based emotional systems.

### CFT

CFT is an evolution-informed, biopsychosocial therapy model, which was developed by Gilbert [16]. It aims to cultivate compassion in order to alleviate psychological distress. Based on research into the neurophysiology of emotions, at least three types of emotion regulation systems can be distinguished: a threat and protection system, a drive and excitement system, and a soothing and social safeness system [16]. CFT works on addressing imbalances between these three systems. Empirical evidence shows that CFT can reduce negative mental health outcomes such as depression and self-critical thinking, while promoting greater self-compassion and compassion toward others [17-19].

In the context of academic stress, higher self-compassion has been associated with reduced academic stress and improved psychological well-being among students [20]. Similarly, Kotera et al [21] found that self-compassion was a significant predictor of better mental health (ie, decrease in symptoms of anxiety and depression) among UK social work students. Compassion-based interventions have also been shown to enhance resilience and reduce distress in student nurses [22], as well as to improve self-criticism, compassion, depression, anxiety, and shame in Chinese international students in South Korea [23]. These findings provide empirical evidence for applying compassion-focused interventions to student populations experiencing academic stress.

### Single-Session Interventions (SSIs)

As the university setting is characterized by high demands and limited resources, brief, scalable, and accessible programs appear particularly suitable. Online single-session interventions (SSIs) are brief, structured psychological programs delivered in one sitting or during one contact with an online program. They are designed to provide immediate support or skills training for specific mental health concerns [24] and have shown positive effects in multiple mental health contexts. For example, Schleider et al [25] found that a single online SSI reduced depressive symptoms and feelings of hopelessness in adolescents, while increasing their sense of agency. The effects were observed for up to three months. Further, a meta-analysis found SSIs to be associated with significant beneficial effects across psychiatric problems in youth [26]. Although SSIs have generally been shown to improve mental health outcomes [25], their application to stress reduction in higher-education settings remains unexplored.

### Research Gap

Despite the high prevalence of psychological distress among university students [8], randomized controlled trials testing low-threshold, accessible, and scalable interventions specifically targeting academic stress remain rare. Most existing interventions are relatively time-intensive, typically involving multiple sessions over several weeks [14,15]. The potential of compassion-focused approaches in this context is largely untapped, especially when they are delivered digitally in a single session. Addressing this gap is critical for developing evidence-based, accessible, cost-effective strategies to support mental health in student populations.

### Research Objectives and Hypotheses

The primary objective is to evaluate the effectiveness of a compassion-focused online SSI in reducing self-reported stress among university students. The secondary objective is to evaluate the effectiveness of the SSI in reducing depressive symptoms and anxiety. The study will test four hypotheses: (1) The intervention group will show a greater reduction in perceived self-reported stress (DASS-21 stress scale) from baseline to 1-week follow-up than the waitlist control group, (2) the intervention group will show a greater reduction in depressive symptoms (DASS-21 depression scale) than the waitlist control group from baseline to 1-week follow-up, (3) the intervention group will show a greater reduction in symptoms of anxiety (DASS-21 anxiety scale) than the waitlist control group from baseline to 1-week follow-up. Furthermore, we expect that (4) the intervention group will report higher improvements in self-compassion from baseline to postintervention and 1-week follow-up compared to the waitlist control group.

## Methods

### Trial Design

This design is a randomized, controlled, parallel-group trial with 2 arms (intervention vs waitlist control) (Figure 1). No additional interventions will be provided beyond the intervention itself during the research period. Assessments will be carried out at baseline (T0), 24 hours after the intervention (T1), and at 1-week follow-up (T2). The trial protocol has been registered at the Open Science Framework [27] and the German Clinical Trial Register (Identifying number DRKS00038409), including prespecified outcomes and a statistical analysis plan (Figure 1).

**Figure 1. F1:**
[figure not shown]
Overview of the trial. DASS-21: Depression, Anxiety, and Stress Scale - 21 items, SCS-D-KF: German 12-Item Short Form of the Self-Compassion Scale, VAS Stress: Visual Analogue Scale Stress.

### Ethical Considerations

The research plan version 1 (August 31, 2025) and informed consent form were approved by the Ethics Committee of the Faculty of Psychology at the University of Basel, Switzerland, with the ethics case number 029-25-1 on September 15, 2025. On October 30, 2025, an amendment to research plan version 1 (October 23, 2025), introducing an additional inclusion criterion to ensure that participants present with a measurable level of stress at baseline, was approved by the responsible ethics committee (ethics case number 029-25-2) prior to study commencement. Any further protocol amendments will be submitted to the responsible ethics committee for approval and will be transparently communicated. The principal investigators (DB and OB) are responsible for updating the trial registration in the German Clinical Trials Register and ensuring that all relevant parties are informed, as required.

To ensure confidentiality and data security, all study-related data will be stored on a restricted-access server. The server is managed by the Faculty of Psychology’s IT department. Data will be pseudoanonymized by assigning a unique study ID upon enrollment; no personally identifiable information will be stored permanently. The online questionnaires will have built-in checks to ensure all items are completed before submission, minimizing missing data.

During the informed consent, participants will be informed that the two principal investigators (DB and OB), both licensed psychotherapists, may be contacted at any time should questions arise or if psychological discomfort related to participation exceeds a level that they feel comfortable handling independently. Additionally, before each exercise of the intervention, a safety note advises that focusing on internal sensations may temporarily increase discomfort for some individuals and recommends pausing the practice if deemed necessary. Given the minimal-risk, single-session, automated, and self-guided nature of the intervention, adverse events will not be systematically assessed. Participants will be informed that they may discontinue participation at any time and may contact the principal investigators if they experience any concerns or unintended effects. If needed, participants will receive guidance on how to access appropriate psychological support.

Participants will not receive direct monetary compensation, but they will have the opportunity to enter a raffle at the end of the study. Twenty winners will be selected at random, and each will receive a book voucher worth 50 CHF (US $64.02). Participation in the raffle will be voluntary, and winners will be contacted via email once data collection is complete. The use of book vouchers as study incentives is well justified, as meta-analytic evidence suggests that material incentives increase both response and retention rates in web-based studies [28,29].

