### Statistical Methods

Analyses will follow a complete-case per-protocol (CC-PP) approach, including only participants who completed T0, T1, and T2 (complete cases). Inclusion and exclusion criteria for PP are prespecified in the protocol. Linear models in combination with type II ANOVA will be applied to investigate group differences for the primary and secondary outcomes.

The primary outcome is the change in perceived stress (DASS-21 stress scale) from baseline (T0) to 1-week follow-up (T2). Secondary outcomes are (1) change in depression (DASS-21 depression scale) from T0 to T2, and (2) change in anxiety (DASS-21 anxiety scale) from T0 to T2. Group allocation (intervention vs waitlist control) will be included as a between-subject factor.

For the additional outcome self-compassion (SCS-D-KF) (3), which is assessed at T0, T1, and T2, a linear mixed-effects model will be used, including visit (T1 and T2) as a within-subject factor and group as a between-subject factor. Subject ID will be included as a random effect to account for within-subject correlations across visits. Baseline self-compassion (T0) will be included as a covariate to adjust for individual differences at study entry.

Covariates (sex, age, and academic level) will be entered as main effects and as 2-way interactions with group. Nonsignificant interaction terms will be removed from the final model. If significant interactions are detected, post hoc tests will be conducted to explore and describe the effects.

Group differences in change scores of the Visual Analogue Scale stress from T0 to directly after the intervention will be analyzed as a manipulation check to assess whether the intervention produced the expected immediate effect on perceived stress.

Results will be reported as mean (SDs) for the intervention and control groups, 2-sided *P* values, and adjusted between-group differences with 95% CIs. For the secondary outcomes, the significance level will be adjusted using a Bonferroni correction for the number of independent tests. Effect sizes will be expressed as Cohen *d*, derived from the *t* values of the models and adjusted for covariates. By convention, *d*=0.2 will be interpreted as a small effect, *d*=0.5 as a medium effect, and *d*=0.8 as a large effect.

All analyses will be performed using R (version 4.5.X; R Development Core Team) [31].

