## Results

As of April 15, 2026, 67 participants have been enrolled. The CONSORT (Consolidated Standards of Reporting Trials) flow diagram is shown in Figure 3. Data collection will conclude once the target sample size of 156 completed cases is reached or 172 participants have been enrolled and ended their participation, after which data analysis will begin immediately. As the study does not include clinical populations and is of minimal risk, no interim analyses or stopping guidelines are planned. Results will be published after data collection, presented at scientific conferences, posted on the German Clinical Trials Register (DRKS00038409), and made available as a preprint. The principal investigators (DB and OB) will lead the preparation of the manuscript reporting the trial results. All investigators who contribute substantially to study design, conduct, data analysis, or interpretation will be offered authorship in accordance with International Committee of Medical Journal Editors (ICMJE) guidelines.

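### Harms are deliberately not assessed despite a named risk, and scores already collected are not used to count participants who get worse

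*Protocol article*

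**What the plan says.** Under Ethical Considerations, the article reports that before each exercise "a safety note advises that focusing on internal sensations may temporarily increase discomfort for some individuals". The next sentence states: "Given the minimal-risk, single-session, automated, and self-guided nature of the intervention, adverse events will not be systematically assessed". What remains is a route that the participant must start: they "may contact the principal investigators if they experience any concerns or unintended effects". The article does not say that such contacts will be recorded or reported by arm.

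Under Outcomes, the three DASS-21 scales are measured at T0 and T2 in both arms and analysed as difference scores, with a stated range of 0 to 21 and higher values meaning greater reduction. Under Statistical Methods, the group difference in VAS stress change up to the end of the session "will be analyzed as a manipulation check to assess whether the intervention produced the expected immediate effect on perceived stress". The same section limits the analyses to participants who completed T0, T1 and T2.

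Under Adherence, Retention, and Discontinuation, anyone who stops the intervention is classed as a dropout. Limitations concedes that little will be known about why people stop. The conclusions, in the Abstract and in the Discussion, make scale-up conditional on effectiveness and do not mention harm.

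**The concern.** Low risk is assumed, and that assumption is the reason for not measuring harm. The trial then produces nothing that could check it, although the authors think one risk likely enough to warn about before every exercise.

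The planned uses of the scores do not fill the gap. A difference in mean change can favour the intervention while some participants get worse, and nobody counts them. Someone who stops because an exercise is unpleasant becomes a dropout and, without later assessments, leaves the main analysis. A difference score described as running upward from zero has no place for deterioration.

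At stake is the report rather than the efficacy test. A reader deciding whether to offer the program to students would see an effectiveness estimate with no systematic harm information beside it.

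**Working it through.** **1. Score range (Outcomes).** Each DASS-21 scale has 7 items scored 0 to 3, so a total runs from 0 to 7 × 3 = 21. The difference T0 minus T2 therefore runs from 0 - 21 = -21 to 21 - 0 = +21. The article's 0 to 21 is the range of a single total. If the screening score also serves as T0 (an assumption), eligibility narrows this:
- Stress above 7 means T0 of at least 8, so the difference runs from 8 - 21 = -13 to +21.
- Depression below 10 means T0 of at most 9, so it runs from -21 to +9. For this outcome there is more room to worsen than to improve.

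**2. What a mean difference leaves open.** The Sample Size section assumes d = 0.5. Suppose for illustration that change scores are roughly normal, with equal SDs in the two arms.
- Control mean change 0: the share worsening is Φ(0) = 50% in control and Φ(-0.5) = 31% in the intervention arm.
- Control mean change 0.5 SD (improvement): Φ(-0.5) = 31% and Φ(-1.0) = 16%.

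So the planned benefit is compatible with a sizeable share of the intervention arm scoring worse. Much of that would be ordinary fluctuation, which is why the count must be set beside the waitlist arm and include a margin.

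**3. The trial's own size.** Two-sample t test, two-sided alpha 0.025, d = 0.5, 80% power: 77.3, so 78 per group and 156 in total (power 80.4% at 78). The stated 156 reproduces. The point involves no sample size error, and the fix does not change N.

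**4. What a worsening count could show at this size.** The article gives no harm rates, so the rates below are assumptions.
- Upper limit for zero events, one-sided 95%: 1 - 0.05^(1/n). For n = 78 this is 3.8%; for n = 86 (randomised per group), 3.4%.
- Chance of seeing at least one event among 78, 1 - (1 - p)^78: 54% at p = 1%, 79% at 2%, 98% at 5%.
- Power to compare arms at 78 per arm, two-sided alpha 0.05:

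| Assumed rates | Power |
|---|---|
| 5% vs 10% | 22% |
| 5% vs 15% | 55% |
| 10% vs 20% | 42% |
| 5% vs 20% | 82% |

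- With equal true rates of 5% or 10%, the 95% interval for the difference has a half-width of 1.96 × √(2p(1 - p)/78) = 6.8 or 9.4 percentage points.

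The summary would reveal common worsening and describe it by arm. It would not establish safety.

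**The case against.** Several objections stand.

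- The waiver is stated openly, and the research plan had ethics approval. Participants can reach two licensed psychotherapists, see a safety note before each exercise and are offered guidance to support. Eligibility asks for healthy students and excludes DASS-21 depression of 10 or more and a score of 2 or more on item 21.
- The scores fit the named risk imperfectly. DASS-21 at one week cannot show transient discomfort during an exercise. VAS stress measures stress rather than discomfort, and someone who stops midway may not provide the rating. The waitlist arm has no session in that window, so its VAS comparator is unclear.
- A registered analysis plan exists but is not shown, and it could contain worsening tables. The decision not to assess adverse events, however, is stated in the article itself and is not left to that plan.
- Attrition is examined by logistic regression, and an intention-to-treat mixed model is planned as a sensitivity analysis. The first does not give reasons for stopping, and the second is again a comparison of means.

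Three stronger readings are tempting and unsupported. A reader might infer that the trial plans to conclude that risk is minimal. It does not: minimal risk is a design premise, and the scale-up statement makes no safety claim, so it is incomplete on harm rather than contradicted. A reader might also infer that the waiver rests on the absence of clinical populations. That phrase justifies a different decision: "As the study does not include clinical populations and is of minimal risk, no interim analyses or stopping guidelines are planned". The waiver cites only the nature of the intervention, so its population wording need not be rewritten on this ground. Finally, a reader might try to bound undetected harm by assuming what share of events participants report unprompted. The article gives no such share, so no bound of that kind is evidence here.

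**Conclusion.** The point holds in a limited form. The article chooses not to assess harms systematically directly after naming one, and its stated analyses would not count participants who worsen. The stated difference-score range is wrong on its face: -21 to +21, not 0 to 21. The efficacy test and the sample size of 156 are unaffected.

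The gain from the fix is modest: an upper limit near 3.8% if no events are seen among 78, and adequate power to compare arms only for a large excess (82% for 5% versus 20%). These figures rest on assumed event rates and on 78 participants per arm with scores. This is a change the sponsor should make for the sake of the report; it is not a flaw that invalidates the trial.

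**What to change.** Amend Ethical Considerations and Statistical Methods to add a descriptive harm summary by randomised arm, covering everyone with the relevant scores and not only completers of all three assessments:

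- number and proportion with any increase, and with an increase beyond a margin fixed before unblinding, in DASS-21 stress, depression and anxiety from T0 to T2;
- the same for VAS stress from T0 to directly after the session, for the arms in which it is collected;
- counts of discontinuations and of contacts to the principal investigators.

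Under Outcomes, correct the difference-score range to -21 to +21. In the conclusions, limit the scale-up statement to effectiveness, and say that these measures describe worsening, do not establish safety and capture transient discomfort only in part.

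The cost is a few tables, a simple record of contacts, and a minor amendment to the ethics committee and the registry. No visit, questionnaire or participant is added. The downsides are low power to compare arms and some natural fluctuation counted as worsening, which the waitlist arm helps to calibrate for the DASS-21. With 67 of 172 enrolled on April 15, 2026 and analysis planned for winter 2026, the summary could still be fixed in advance of the analysis.
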